#### Scale of Measurement - Tests

The different instruments used are detailed in Table 3 (58–79). We elected to assess the intervention program at 4 and 24 months to use the same scales at both stages of the child's development. If not possible, two different scales are used in the assessments at 4 and 24 months (EPDS-BDI), and they present a good correlation (91). The choice of tests has proven restrictive given the criteria used, namely a validated test in French, and without specific and extended training (92, 93).

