### Objectives of the PERL Study

The main objectives are to assess the effects of regular preventive HVs performed by PMI nurses on the prevalence of developmental and language delays in children, by comparing intervention and control groups.

The secondary objective is to longitudinally analyze the impact of the intervention for each family over the child's fourth to 24th months. The impact will be studied through the evolution of the child's development, looking at therapeutic alliance, parental feelings about the intervention and maternal mental health, quality of mother-child interactions, and experience of parenting.

PERL is an intervention system because a professional accompanies the family with tailored support. It is also a prevention system because this intervention begins before any disorder or diagnosis of delay. The goal in terms of mental health protection is to reduce the incidence of disorder by eliminating or reducing risk factors, and by intervening before symptoms develop. We propose with PERL a primary prevention program through intervention.

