					**Mths after birth years**					
Neonatal Brazelton Assessment Scale (NBAS)	Neonatal behavior (0–1 month)	Brazelton e (58) (3° ed)	Psychologist at the maternity hospital/home visit	The assessment concerns: autonomic system motor tone organization state organization and regulation early interaction	X				X	X
Brunet-Lézine Revised Developmental test	Child development (2–30 months)	Brunet and Lézine, 1965 (59)	Psychologist during home visits	Developmental age (developmental quotient)4 dimensions: Language Social relationships Motor gross Motor fine 30 item test scored partly		X	X		X	X
Alarm Baby Distress scale (ADBB)	Sustained withdrawal behavior (2–24 months)	Original scale in FrenchGuedeney and Fermanian (60) in France	Psychologist, after home visits, with video	8 items, 5 point Likert scale (0–4), range 0–32 Withdrawal behavior if ≥ 5		X	X		X	X
Symptom Check-list (SCL-90)	Mother's psychological disorders	Derogatis (61) Translation	Mother during home visits	90 items, 5 point-Likert scales (0–4) X X X10 subscales: Somatization (0–48) Obsessive-Compulsive (0–40) Interpersonal Sensitivity (0–36) Depression (0–52) Anxiety (0–40) Hostility (0–24) Phobic Anxiety (0–32) Paranoid Ideation (0–24) Psychoticism (0–40) Other symptoms (0–28) Higher scores indicate greater Clinical impairment.		X	X		X	X
Working Alliance Inventory (WAI)	Working alliance between the mother and the pediatric nurse	Horvath and Greenberg (62) French validation Guedeney et al. (63)	Mother and pediatric nurse after home visits	12 items, Likert scale (1–7) Range 12–84 Higher scores indicates better working alliance		X	X		X	
Attachment Q-Sort (AQS)	Child's attachment (10 months−3 years)	Waters and Deane (64) French translation made and validated by a panel of infant mental health experts (65)	Assessment team (psychologist and nurse) after home visits	Two rates assess each situation during a home visit of 2 h90 itemsCorrelation with typical secure pattern: Insecure attachment if <0.35 Secure attachment if ≥ 0.35			X		X	X
Edinburgh Postnatal Depression Scale (EPDS)	Self-Assessment of postpartum depression	Cox et al. (66) French validation: Guedeney and Fermanian (67)	Mother during home visits	10 items, 4 point-Likert scales (0–3) Range 0–30 Higher scores indicate higher levels of depressive symptoms.		X			X	X

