Bobigny's early interactions grid	Mother-infant interactions (0–4 years)	Devised by experts in infant mental health and specifically perinatal consultations, 1989 (68)	Psychologist after home visits	Qualitative assessment grid describing the quality of the interactions and the dominant mode of interaction.		X	X		X	X
Mini Q-SORT	Maternal sensitivity	Pederson and Moran (69) Suited to analysis of short video sequences Tarabulsy and et al. (70)	Psychologist after home visits (video)	Sorting of 25 cards describing maternal behavior according to a Q-sort procedure		X	X		X	X
Beck Depression Inventory (BDI)	Maternal depression	Validated by Beck et al. in 1961 (71) Version abridged by Beck et al. in 72 (72) Translated and validated in French by Delay and Pichot in 1963 and 1964 (73, 74) Abridged version validated by Reynolds and Gould et al. in 1981 (75)	Mother during home visits	13 items 4-point Likert scales Range 0–39 Higher scores indicate higher levels of depressive symptoms. 4: no depression; 4–7: mild depression; 8–15: moderate depression; 16+: severe depression			X		X	X
Family Affluence Scale (FAS) form	Socio-economic status of the families		Mother during home visits	4 questions to tick: yes/no and enter number		X	X		X	X
Brief Infant-Toddler Social and Emotional Assessment (BITSEA)	Early screening for delays in social and emotional competencies (1–3 years)	Validated by Briggs-Gowan and Carter and (76) Translated by Wendland and Saïs, 2010 and validated in French by Wendland et al. (77)	Mother during home visits	42-item questionnaire 3-point Likert scales (0–2) Provides indications on the social-emotional profile and competencies of children according to their parents.			X		X	X
Parenting representations interview (PRI)	To obtain parents' representations concerning their child, themselves as parents and their experience of the intervention	Questions taken from the R interview drawn up by Lebovici et al. (78)	Mother during home visits	Semi-structured interview 4 questions. The themes are: description of their child, themselves as parents, their reaction to their child's crying, and their experience of the support and home intervention as part of the research		X	X		X	X

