#### Longitudinal Assessment

A longitudinal assessment will be carried out for both groups to measure the evolution of the test scores from the fourth to the 24th month. A Cox model will be used, with the baby's development (under/over average development) as principal judgment criteria.

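### The EPDS at 4 months and the BDI at 24 months cannot give a change in maternal depression, and good correlation does not make them a repeated measure; the SCL-90 Depression subscale can fill that role

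*Protocol article*

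**What the plan says.** Under Scale of Measurement - Tests, the article gives its design principle: "We elected to assess the intervention program at 4 and 24 months to use the same scales at both stages of the child's development". Where that could not be done, it says, "two different scales are used in the assessments at 4 and 24 months (EPDS-BDI), and they present a good correlation (91". It gives no coefficient, and no other reason why this pair can stand in for a repeated scale.

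Table 3 (Evaluation in Both Groups) schedules three instruments that bear on maternal depression, all in both groups:

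- EPDS, at 4 months only: "10 items, 4 point-Likert scales (0–3) Range 0–30".
- BDI, abridged version, at 24 months only: "13 items 4-point Likert scales Range 0–39".
- SCL-90, at 4 and 24 months, with a depression subscale among its ten: "Interpersonal Sensitivity (0–36) Depression (0–52) Anxiety (0–40".

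Two other sections call for change over time. Objectives of the PERL Study states: "The secondary objective is to longitudinally analyze the impact of the intervention for each family". The sentence that follows it lists maternal mental health among the aspects to be studied. Longitudinal Assessment plans, for both groups, to "measure the evolution of the test scores from the fourth to the 24th month".

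The maternal mental health hypothesis, in Outline of the Trial and Hypotheses, is a different kind of statement. It expects less depression in the intervention group at 24 months, which is a between-group comparison at one age.

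**The concern.** The article puts the EPDS-BDI pair in the place of a scale given twice and defends this by correlation alone. Correlation says that mothers who rank high on one scale tend to rank high on the other. It does not say that a given score on one corresponds to any particular score on the other. A difference between a BDI at 24 months and an EPDS at 4 months therefore mixes change in the mother with change of instrument, and the two cannot be separated without a conversion table, which the article does not mention.

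At stake is the depression part of the secondary longitudinal objective. If the analysis followed the stated rationale, it could report a rise or fall in depressive symptoms that comes from the scales. The trial already collects a measure that avoids this, but the article does not name it for the purpose.

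**Working it through.** **Inputs.** From Table 3: EPDS 10 items scored 0–3, so 10 × 3 = 30; BDI 13 items on four points with range 0–39, so 13 × 3 = 39; SCL-90 Depression subscale 0–52. The article gives no figure for the EPDS-BDI correlation, so there is none to reproduce on this point.

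**Step 1: correlation carries no information about metric.** For any constants a and b > 0, corr(E, a + bB) = corr(E, B). The mean of (a + bB) − E, however, depends on both a and b. A high correlation is therefore compatible with any mean difference between the two scales.

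**Step 2: raw difference at equal relative severity.** Take a mother at the same fraction f of the maximum on both scales. The apparent change is 39f − 30f = 9f.

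| f | EPDS (30f) | BDI (39f) | Apparent change (9f) |
|---|---|---|---|
| 10% | 3.0 | 3.9 | +0.9 |
| 20% | 6.0 | 7.8 | +1.8 |
| 30% | 9.0 | 11.7 | +2.7 |
| 40% | 12.0 | 15.6 | +3.6 |

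Equal fraction of the maximum is only one possible sense of equal severity. It is used here to show that the ranges alone produce a change, not to estimate a bias.

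**Step 3: illustration with assumed parameters.** For 128 simulated mothers, EPDS-like severity was drawn with mean 10 and SD 4. The BDI-like score was 1.3 × (severity + shift) plus noise with SD 3, where 1.3 = 39/30. The shift is the true change.

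| True shift | Correlation | Raw mean BDI − EPDS | Mean change in z-scores |
|---|---|---|---|
| 0 | 0.849 | +2.51 | 0 |
| −3 | 0.849 | −1.39 | 0 |
| +3 | 0.849 | +6.41 | 0 |

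The raw means differ by 1.3 × 3 = 3.9 from the no-change row, as they should (2.51 − 3.9 = −1.39; 2.51 + 3.9 = 6.41). The no-change row is itself +2.51. The correlation is identical in all three rows, so it cannot tell improvement from worsening.

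**Step 4: standardising does not repair it.** If each scale is converted to z-scores in the whole sample at its own age, the mean z is 0 at 4 months and 0 at 24 months by construction, and the mean change is 0 − 0 = 0 whatever happened. A difference between groups in z-change can still be computed. It equals the standardised group difference at 24 months minus that at 4 months, so it compares two contrasts on two instruments. It does not show whether mothers in either group improved.

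**Step 5: what is not affected.**

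- Sample size. Two-sided 5%, 80% power, 50% against 25%: n = [1.96 × √(2 × 0.375 × 0.625) + 0.8416 × √(0.25 + 0.1875)]² / 0.25² = (1.342 + 0.557)² / 0.0625 ≈ 57.7, so 58 per group, as the article states. No depression scale enters.
- Between-group BDI comparison at 24 months. One scale, one age, both groups. The detectable standardised difference at 80% power is (1.96 + 0.8416) × √(2/n), which is 0.52 at 58 per group and 0.50 at 64.

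**Step 6: the common measure.** The SCL-90 Depression subscale has one range, 0–52, at both ages in both groups, so a within-mother difference is defined on a single metric.

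**The case against.** The strongest reply is that the article nowhere says EPDS and BDI scores will be subtracted, pooled or modelled as one repeated measure. The planned evolution of scores can be read as covering only tests given at both ages, and the one model named in that section concerns the baby's development. The instrument choice is also explained in part: the article describes the EPDS as a postpartum scale and says selection was limited by French validation and training needs. The depression hypothesis is a 24-month comparison, which the BDI serves alone.

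Most of this stands, and it limits the point. Three stronger readings are tempting, and the document supports none of them:

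- A reader might infer that no change in depression can be measured in this trial. Table 3 contradicts that, because the SCL-90 Depression subscale is taken at both ages in both groups.
- A reader might infer that the plan treats the two scales as interchangeable scores. The text offers correlation as reassurance and does not state such a use.
- A reader might size the problem by squaring a correlation and calling the remainder instrument difference. No coefficient is given, the unexplained variance also contains ordinary measurement error, and correlation does not capture a difference in metric.

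The stated rationale itself does not survive the reply. The article sets out to repeat the same scales, names this pair as the exception, and gives correlation as the reason it is acceptable, while two other sections promise change from 4 to 24 months. This is a stated reason that does not support the purpose, not a detail left to a fuller document.

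**Conclusion.** The point holds in a limited form. Change in maternal depression from 4 to 24 months cannot be measured from the EPDS-BDI pair, and the correlation offered does not justify using it so. This follows from the invariance of correlation and the Table 3 ranges, and needs no assumption about the size of the correlation. The simulated values are illustrative only, and no bias in a planned analysis is estimated, because no EPDS-to-BDI change is explicitly planned.

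The consequence is confined to the depression part of one secondary objective. It is a minor point and a free improvement.

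**What to change.** In Scale of Measurement - Tests and Longitudinal Assessment, state that:

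- change in depressive symptoms from 4 to 24 months is based on the SCL-90 Depression subscale (0–52), already scheduled at both ages in both groups;
- EPDS at 4 months and BDI at 24 months are each compared between groups separately, at their own age;
- no EPDS-to-BDI change, raw or standardised, is formed, and the correlation is not cited as support for one.

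An analysis of BDI at 24 months adjusted for EPDS at 4 months is acceptable, because a covariate need not share the outcome's metric. The monthly visits start at birth, so the 4-month EPDS is not a pre-intervention value. The adjusted result should therefore be read as the group difference given the mother's state at 4 months, and shown beside the unadjusted comparison.

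The cost is a few sentences of wording. No new data, visits or participants are needed. The article places the comparative analysis after the 24-month evaluations are complete, so under that timetable the wording can be settled before the analysis starts.

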#### Socio-Demographic and Family Data

Socio-demographic and family data are collected for both groups: age, level of education, occupation, and family situation, for both parents. For the child: gestational age, gender, birth order within siblings, and birth weight. Information is collected on type of birth, child care arrangements, school attendance, and age on starting school, whether planned or unplanned birth, feeding (breast or bottle), father's involvement in the PERL study, whether or not the family is receiving other support measures, etc. Finally, birth trauma and the presence of any serious psychopathology in the parent will be scored.

During the interview, SB will record how the parent feels about the child, the way the parent sees themselves as a parent, their responses to crying/opposition from the baby, and parent experience of the intervention. SB collects information about how the parents accommodate regular HV from a PMI nurse and how they benefit from this support.

### Data Analysis

All the conditions of use of the tests will be checked before using them. A significant level is <0.05 for all tests.

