## Abstract

**Background:** Early childhood is a key period for reducing the social inequalities that affect health. Some parenting support and home visitation programs have proven to be effective in assisting parents during this period. France's *Protection Maternelle et Infantile* (maternal and child welfare) services (PMIs) are at the heart of this primary prevention and may adapt their intervention to improve parenting support. In this manuscript, we describe the protocol of the PERL study, an intervention based on a home visiting program.

**Method and design:** The PERL study is a single-center, randomized, controlled interventional trial. The aim was to assess the impact of a preventive home visiting program on the development of young children and parent-baby interaction. Visits were made by PMI nurses to 64 randomly recruited families from the general population. All families who had a baby born after 37 weeks of pregnancy between September 2018 and December 2019, and who resided in the trial area were eligible. Participants were randomly allocated to the intervention group or the control group. The PMI nurses made 12 home visits in the first year, 6 in the second year, and 4 in the third and fourth years of the child's life. Primary and secondary outcomes were measured when the child was 4 and 24 months old. These measurements recorded (i) the child's developmental milestones, in particular, language and socio emotional skills, (ii) early interaction, maternal sensitivity, and attachment patterns, (iii) maternal psychopathology including depression.

**Discussion:** This study aims to assess the impact of home visits, made by specifically-trained and supervised nurses, on the child's development and parent-child interactions. Such interventions are complementary to other preventive programs addressing the impact of social inequalities on perinatal health. Placing nurses' professional skills at the center of this project may prove an effective and cost-saving intervention compared to existing programs. The study proposes a prevention model that is in keeping with the principle of reducing social inequalities in health by providing support from the earliest age through public service.

**Clinical Trial Registration:** The clinical trial number is NCT03506971, registered on April 24, 2018.

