#### Determination of Sample Size

A calculation of sample size was carried out with one case per one control, a power of 80%, an alpha risk of 5%, a global developmental delay (obtained with the BLR test) prevalence rate of 50% in the controls and 25% in the children on the program (based on INTERREG results). The result obtained is a sample of 58 people in the intervention group and 58 in the control group. Taking into account the potential loss of 10% of subjects over the course of this ongoing research, 64 subjects were originally recruited for the intervention group and 64 subjects in the control group.

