The final limitation lies in the small sample size of the study. We are well-aware that, given the small sample size, we may not be able to highlight any significant difference on the primary endpoint but will, however, gain quantitative and qualitative indicators of the impact of this device. In addition, if the results on the scales are not significant, a qualitative analysis of the results will be carried out.

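### The article describes its primary outcome in incompatible ways and judges every test at 0.05, so the 5% alpha behind the sample size is not kept across the main objectives

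*Protocol article*

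**What the plan says.** All references are to the protocol article.

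- **Data Analysis:** "A significant level is <0.05 for all tests". Comparative Analysis then assigns a t-test to quantitative and a chi-squared test to qualitative variables, Correlation Analysis adds Spearman tests, and Longitudinal Assessment adds a Cox model. No test is ranked above another.
- **Objectives of the PERL Study:** two outcomes share the main objective, in these words: "The main objectives are to assess the effects of regular preventive HVs performed by PMI nurses on the prevalence of developmental and language delays".
- **Outline of the Trial and Hypotheses:** less developmental delay is expected at 24 months and less language delay at 4 years.
- **Abstract:** "Primary and secondary outcomes were measured when the child was 4 and 24 months old". Table 3 schedules the language screening test (ERTL 4) at 4 years only, so these ages leave it out.
- **Determination of Sample Size:** the calculation uses global developmental delay on the Brunet-Lézine test (BLR) alone, with a "prevalence rate of 50% in the controls and 25% in the children on the program". No age is given.
- **Data Collection:** assessments are concentrated at 24 months to serve a primary objective, in the singular.
- **Longitudinal Assessment:** the main criterion is development below or above average, in a Cox model.
- **Strengths and Limitations:** one primary endpoint is mentioned without being named. The section then adds: "if the results on the scales are not significant, a qualitative analysis of the results will be carried out".

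**The concern.** A 5% error rate belongs to a defined test. Here the reader cannot tell whether the trial's verdict rests on developmental delay at 24 months, on language delay at 4 years, on either of them, or on development at 4 as well as 24 months. Clinical and Research Implications plans a comparative analysis from 2022 and a final one in 2024–2025, so the two main outcomes are also read at different times. If either may count as the main result, the 5% used to size the trial is not the error rate of the conclusion.

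The qualitative step is a separate matter. An analysis carried out only when the scales are not significant can add support for the programme after a null result, but can never temper a positive one. The article says that, depending on the outcomes, it aims to propose the model for national use, so how the verdict is reached matters.

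**Working it through.** **1. Reproduce the sample size.** Inputs from Determination of Sample Size: control rate 0.50, intervention rate 0.25, power 80%, alpha 5%, allocation 1:1. Sidedness is not stated; two-sided is assumed.

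Formula, pooled variance under the null, no continuity correction:

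n = [z(0.975)·√(2·p̄·q̄) + z(0.80)·√(p1·q1 + p2·q2)]² / (p1 − p2)²

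- p̄ = 0.375, so 2·p̄·q̄ = 0.46875, root 0.6847; times 1.960 = 1.342
- p1·q1 + p2·q2 = 0.25 + 0.1875 = 0.4375, root 0.6614; times 0.8416 = 0.557
- (1.342 + 0.557)² / 0.0625 ≈ 57.7, rounded up to **58 per group**

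This matches the article: "The result obtained is a sample of 58 people in the intervention group and 58 in the control group". A one-sided test would give 46. With 10% added, 58 × 1.1 = 63.8, or 64, as stated. So the trial is sized for one two-sided test at 5%, on one outcome.

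**2. Error rate over the two main outcomes, each at 0.05.**

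- Independent: 1 − 0.95² = **9.75%**
- Correlated (bivariate normal test statistics; correlations assumed, as the article gives none): 9.1% at 0.5, **7.0%** at 0.9
- If BLR at 4 months also counts as primary, as the abstract allows, there are three tests: 1 − 0.95³ = 14.3% if independent

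**3. Counting only false results that favour the intervention.** One two-sided 5% test puts 2.5% in that direction.

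- Two independent tests: 1 − 0.975² = **4.9%**
- At correlation 0.5: 4.5%; at 0.9: 3.5%

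**4. All between-group comparisons in Table 3.** Family affluence, the alliance scale (intervention group only), the neonatal scale and the interview are left out.

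- At 4 months, one per instrument: BLR, ADBB, SCL-90, EPDS, Bobigny grid, Mini Q-Sort = 6
- At 24 months: BLR, ADBB, SCL-90, AQS, Bobigny grid, Mini Q-Sort, BDI, BITSEA = 8
- At 4 years: ERTL 4 = 1
- Total 15; expected chance findings with no effect: 15 × 0.05 = **0.75**
- With BLR as a global score plus 4 dimensions (+4 at each age) and SCL-90 as 10 subscales (+9 at each age): 15 + 8 + 18 = 41; 41 × 0.05 = **about 2**

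These totals include the two main tests; without them they are 13 (0.65) and 39 (1.95). The expected number does not depend on correlation. Spearman and Cox tests would come on top.

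**5. Cost of keeping two primary outcomes.** At 0.025 each, the error rate is at most 5% (4.94% if independent). BLR would then need 70 per group, or 78 after 10% loss (70 / 0.9), and its power at 58 per group would fall from 80.2% to 71.2%.

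**The case against.** The strongest reply is that the article leans towards one primary outcome. The sample size uses BLR delay only, Data Collection ties a single primary objective to 24 months, Longitudinal Assessment takes the baby's development as its main criterion, the limitations speak of one endpoint, and the abstract's ages exclude ERTL 4. If BLR delay at 24 months is the sole primary outcome, that test keeps its 5%. This stands as evidence of intent. It does not settle the matter, because the objectives still list language delay as a main outcome, the abstract adds 4 months, and the Cox analysis is not the comparison of two proportions on which the trial was sized.

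A second reply is that a condensed article may leave multiplicity rules to an analysis plan. That is fair for the handling of secondary scales, whose lack of adjustment is not the point here. The contradiction over the primary outcome, and the single level set for all tests, are stated in the article itself.

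A reader might also infer stronger things that the documents do not support:

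- **That any significant secondary scale may be claimed as success.** No section says so, and main and secondary objectives are separated.
- **That a false claim of benefit on the main outcomes is well above 5% likely.** In that direction it is at most about 4.9% for independent or positively correlated tests.
- **That all of the roughly 40 comparisons are efficacy claims.** No hypothesis is stated at 4 months, and the 4-month scores are grouped with population characteristics and group homogeneity. The Bobigny grid is described as qualitative. The hypotheses themselves number about ten, giving 10 × 0.05 = 0.5 expected chance findings.
- **That the qualitative analysis inflates type I error, or may overturn a null result.** It does not change the error rate, and the article openly allows that the primary comparison may not be significant.

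**Conclusion.** The point holds as a contradiction with a moderate, quantifiable consequence. The article supports at least three readings of the primary outcome: two main outcomes at 24 months and 4 years, primary outcomes at 4 and 24 months, or one unnamed endpoint. With every test at 0.05 and no order among them, the 5% used for the sample size is not kept across the main objectives. The two-sided rate is 9.75% if the two tests are independent and about 7% at correlation 0.9; in the favourable direction it is up to about 4.9%, against 2.5%. The correlations are assumptions, and the two-sided rate exceeds 5% unless the tests are perfectly correlated.

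The wider set of comparisons would produce roughly 0.75 to 2 chance findings with no effect, depending on whether subscales are counted. This bears on how secondary results are read, not on the primary verdict. The conditional qualitative analysis is a one-sided route of interpretation, with no numerical effect on type I error.

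**What to change.** - Name global developmental delay on the BLR at 24 months, the outcome on which the trial was sized, as the single primary outcome, tested once at 0.05 as a comparison of two proportions.
- Align the Abstract, Objectives, Longitudinal Assessment and Strengths and Limitations with that choice, and add the age to the sample size section.
- Treat ERTL 4 at 4 years and all other scales as secondary, reported with 95% confidence intervals and not able to support a stand-alone efficacy claim. Testing ERTL 4 at 0.05 only if the primary is significant is one acceptable option among several, and fits the article's calendar.
- Carry out the qualitative analysis whatever the quantitative result, and state that it cannot change the verdict on the primary outcome.

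The cost is a few sentences. They carry weight as pre-specification only if they are fixed before the 24-month group comparison, planned for 2022. The target of 58 per group and the 5% level stay as they are. The real price is that language delay at 4 years loses its status as a main outcome. If the sponsor wants to keep both, the alpha must be shared, with the loss of power shown above.
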